#### Baseline parameters

During their first visit to the emergency department or urgent care center, patients are assessed for eligibility. If informed consent is obtained, parameters regarding demographics, medical history, and injury are collected. Radiographic images and/or clinical pictures are taken as per local standard of care (routine) procedures. Demographic data, such as age, sex, height, weight, and ethnicity, are recorded. Medical history is documented in sufficient detail to calculate the Charlson Comorbidity Index, which has been designed and validated to classify prognostic comorbidity in longitudinal studies [11, 12]. Its prognostic accuracy has also been validated for a combined age-comorbidity index [13]. The recorded information includes the history of cardiovascular diseases, asthma, chronic lung disease, diabetes, renal disease, chronic liver disease, gastric or peptic ulcers, cancer, dementia, rheumatic or connective tissue disease, immunocompromised status [human immunodeficiency virus and/or others], and American Society of Anesthesiologists scores.

Information on medication history comprises the use of antibiotics, osteoporosis treatment, chronic use of analgesics and/or corticosteroids, and alcohol and drug intake. Information concerning the injury includes which side of the body the fracture is located on, high- or low-energy trauma, injury severity score, and fracture classification according to the AO/OTA fracture and dislocation classification [14]. Detailed information on additional fractures of the lower extremities both ipsilateral and contralateral will be collected. Furthermore, details of additional injuries will also be collected (e.g. cerebral, spine, thorax, abdomen, pelvis, upper extremity). Soft-tissue injury is to be classified according to Tscherne [15] for closed fractures and according to Gustilo-Anderson [16] and the OTA Open Fracture Classification [17] for open fractures. Concomitant fractures of the tibia or fibula are to be classified according to the AO/OTA fracture and dislocation classification [14].

#### Interventions and study procedures

Patients will undergo fracture fixation using osteosynthesis, including single- or multiple-staged procedures (e.g., initial external fixation with later conversion to internal fixation). The operative treatment for TSFs in adults mainly depends on the fracture characteristics and extent of the soft tissue damage and is to be performed according to the standard (routine) care procedures based on the individual clinician’s judgment and patient characteristics. Neither specific treatment nor specific time points for FU visits are dictated for registry purposes.

Registry-related assessments will include radiographic evaluations, performed by the treating surgeon at the treatment visit and at defined time points after treatment, following each site’s standard (routine) visit schedule for up to 36 months. Radiographic images and/or clinical pictures will be stored to enable future ad-hoc analysis after de-identification. If patients are unable to attend the last planned FU visit, they will be contacted by e-mail or phone to document the final outcomes, especially patient-reported outcomes (PROs) and complications not previously captured. The planned registry schedule is displayed in Table 2 over the 36-months FU visit period.

**Table 2 Tab2:** Registry schedule for the Fracture-Related Outcome Study for operatively treated Tibia shaft fractures (F.R.O.S.T.)

	Baseline	Treatment	Post-treatment visit 1^a^	Post-treatment visit 2^a^	Post-treatment visit 3^a^	Additional Post-treatment visit(s)^a^
	–	Day 0	6 weeks (target 42 days: range 14 to 105)	6 months (target 183 days; range 106 to 260)	12 months (target 365 days, range 261 to 456)	Up to 36 months
Eligibility	X					
Patient information/consent	X^b^					
Demographics	X					
Medical history and pre-treatment values	X					
Injury(s) details	X					
Treatment details		X^c^				
Clinical outcome(s)			X	X	X	X
Patient-reported outcome(s)						
PROMIS: Global Health	X		X	X	X	X
PROMIS: Physical Function	X		X	X	X	X
PROMIS: Pain Interference			X	X	X	X
Pain numeric rating scale (NRS)			X	X	X	X
Complications			X	X	X	X
Images and/or other clinical pictures	X^d^	X^d^	X^d^	X^d^	X^d^	X^d^

^a^ If a patient does not visit at the specified time point, the visits will be assigned according to the specified rules. Additional postoperative visits may take place up to 36 months after day 0

^b^ Informed consent may occur after treatment under certain circumstances (see details in section 10). No data can be collected in the eCRF prior to consent

^c^ Treatment may occur on the same day as the baseline. Treatment of tibial fractures may require two or more stage-procedures (e.g., external fixation and secondary internal fixation) performed on different days

^d^ Images (X-ray images, CT scans, etc.) and clinical pictures are collected ONLY if they are taken as part of the standard of care (routine) procedures. All images and photographs will be de-identified

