**Methods:**

This prospective, international, multicenter, observational registry for TSFs was recently developed. Recruitment started in 2019 and is planned to take 36 months, seeking to enroll a minimum of 1000 patients. The study protocol does not influence the clinical decision-making procedure, implant choice, or surgical/imaging techniques; these are being performed as per local hospital standard of care. Data collected in this registry include injury specifics, treatment details, clinical outcomes (e.g., FRI), patient-reported outcomes, and procedure- or implant-related adverse events. The minimum follow up is 12 months.

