**Department of Orthopaedics and Traumatology, University Medical Center, Johannes Gutenberg-University, Mainz, Germany** ***(Planned New Site)***	**PI** [name]
**Department of Orthopaedics and Traumatology, Queen Mary Hospital, University of Hong Kong, Pokfulam, Hong Kong** ***(Planned New Site)***	**PI** [name]
**Department of Surgery, Franciscus Gasthuis en Vlietland Hospital, Rotterdam, The Netherlands** ***(Planned New Site)***	**PI** [name]
**Department of Orthopedics, Elisabeth-TweeSteden Hospital, Tilburg, Netherlands** ***(Planned New Site)***	**PI** [name]

Site selection was based on a world-wide open call by the AO Foundation. It was decided that sites should be included from different parts of the world. The following criteria were developed during the decision-making process:

1. A site should be able to recruit a minimum number of patients within the planned recruitment time (a minimum of 65–75 patients per year).

2. A site should make sure that patients are in follow up for a minimum time of 1 year.

3. Sites must be able to anonymize their clinical data (e.g., radiological images).

4. Sites are able to plan patient visits as per standard of care at the site.

5. Sites should agree to the administrative conditions (reimbursement, contracts) and receive approval from their local ethical committee.

6. Sites should be able to perform registry related documentation

*PCI* Principal Coordinating Investigator, *co-PCI* co-Principal Coordinating Investigator, *PI* local Principal Investigator

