The pre-injury status concerning global health and physical function will be captured retrospectively at baseline and entered in the database. The *global health assessment* reflects an individual’s evaluation of their physical, mental, and social health. In this registry, a short form of 10 questions (v1.2) will be used. The *pain interference* questionnaire covers pain interference with physical, social, and recreational activities and will be documented with a short form of 8 questions (v1.0 – Pain Interference 8a). The *physical function (mobility)* questionnaire assesses the patients’ ability to perform various daily living activities, documented in a short form of 10 questions (v2.0 – Physical Function 10b). *Pain* will be documented on a numeric rating scale (NRS) from 0 to 10 for the injured leg, the knee of the injured leg, and the ankle of the injured leg. *Procedure- or implant-related adverse events*, i.e., complications, will only be documented for the injured tibia, but not for concomitant fractures in the fibular, malleolar, or other regions.

In addition to AEs entered via free text, some pre-defined complications will be captured. *Intraoperative pre-defined complications* include iatrogenic fracture, iatrogenic vessel damage, excessive bleeding, iatrogenic nerve damage, and intraoperative resuscitation. *Postoperative pre-defined complications* include compartment syndrome, FRI, nonunion, refracture/peri-implant fracture, secondary loss of reduction, secondary displacement or breakage of the fixation material, deep vein thrombosis, pulmonary embolism, ongoing pain medication, or inability to bear full weight 1 year after definitive treatment.

FRI will be diagnosed as defined in the recently published consensus definition [24] and subsequent update [25]. Additional contextual information will be collected for all AEs and comprises the start date of the event, its severity and seriousness, information about the related additional treatment(s), date of recovery, and the event’s outcome.

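### The 12-month visit is accepted from day 261 and no later contact is required, so the 12-month minimum follow-up is not guaranteed and the 1-year weight-bearing item can be recorded up to 104 days early

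*Protocol article*

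**What the plan says.** All references are to the protocol article.

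- **Length of follow-up.** The abstract (Methods) states: "The minimum follow up is 12 months". The site criteria under Study design repeat this as a duty of the site: "A site should make sure that patients are in follow up for a minimum time of 1 year".
- **Visit windows.** Table 2 (Interventions and study procedures) gives three post-treatment visits: "6 weeks (target 42 days: range 14 to 105" days, "6 months (target 183 days; range 106 to 260" days, and "12 months (target 365 days, range 261 to 456" days. A footnote says that off-schedule visits are assigned by specified rules, and that further visits up to 36 months are possible.
- **Timing follows local routine.** The same section says: "Neither specific treatment nor specific time points for FU visits are dictated for registry purposes".
- **Remote contact.** Patients who cannot attend the last planned visit are reached by e-mail or phone for final outcomes, including complications not yet captured.
- **A complication fixed in time.** The list of postoperative complications under Outcome measures ends with "ongoing pain medication, or inability to bear full weight 1 year after definitive treatment".
- **Denominator.** Under Statistical analyses, complication rates are divided by the total population, whether or not patients dropped out.

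**The concern.** The 12-month minimum and the 1-year complication both depend on patients being observed at about 1 year. The visit that would normally supply that observation is accepted from day 261. Visit 3 is the last one scheduled, and anything after it is optional. The remote contact is triggered by a missed last visit, and a patient who attended on day 261 has not missed it. A patient whose routine care ends then has a filled 12-month slot and, on the printed text, need not be contacted again.

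Two things are at stake, and they run in opposite directions. A patient still recovering on day 261 could be recorded as unable to bear full weight at 1 year, which overstates that item. An infection, nonunion, refracture or implant failure that arises after the last contact never enters the numerator, while the patient stays in the denominator, which understates those rates. Because they affect different outcomes, the two errors do not cancel. Sites keep their own visit schedules, so effective follow-up can also differ by site. That matters for a registry whose stated main purpose is to relate treatment strategies to outcomes.

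**Working it through.** **Inputs (Table 2).** Visit 1: target day 42, range 14 to 105. Visit 2: target 183, range 106 to 260. Visit 3: target 365, range 261 to 456. One month is taken as 365.25/12 = 30.44 days.

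**What the windows do.** They adjoin without gaps (105/106 and 260/261), so together they sort any visit from day 14 to day 456 into a slot. This is a labelling scheme. The midpoint between the 6- and 12-month targets is (183 + 365)/2 = 274, so the cut at 260/261 lies 13 to 14 days before it.

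**Width of the 12-month label.**
- Earliest: 261/30.44 = 8.57 months.
- Latest: 456/30.44 = 14.98 months.
- Early margin: 365 − 261 = 104 days = 3.42 months, or 104/365 = 28.5% of the year.
- Late margin: 456 − 365 = 91 days = 2.99 months.
- Days accepted: 456 − 261 + 1 = 196, of which 104 (53%) fall before day 365.

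**Time origin.** Table 2 counts from day 0, the treatment day. The weight-bearing item counts from definitive treatment. A Table 2 footnote allows stages on different days, and the article does not say which stage is day 0. Assume that day 0 is the first stage and that definitive treatment follows g days later (g is not given). A day-261 visit is then 261 − g days after definitive treatment, and short of 1 year by 104 + g days:

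| g (assumed) | Days after definitive treatment | Short of 365 by |
|---|---|---|
| 0 | 261 | 104 days (3.4 months) |
| 7 | 254 | 111 days (3.6 months) |
| 14 | 247 | 118 days (3.9 months) |
| 28 | 233 | 132 days (4.3 months) |
| 56 | 205 | 160 days (5.3 months) |

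**Lost events.** Suppose a share p of patients has its last contact on day d before 365, and events are spread evenly over the year. The 12-month count is then low by p × (365 − d)/365. If events occur only from day 183 on, the divisor is 365 − 183 = 182. The article gives neither p, nor d, nor the timing of events. As an illustration only, take d = 295 and let p run from 10% to 50%:
- even spread: 0.10 × 70/365 = 1.9% to 0.50 × 70/365 = 9.6%;
- months 6 to 12 only: 0.10 × 70/182 = 3.8% to 0.50 × 70/182 = 19.2%.

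The width of this range shows that the document cannot settle the size.

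**The case against.** The strongest reply is that the window is a labelling rule and has been read as a completion rule. In a registry of routine care, wide adjoining windows are a sensible way to sort visits. No sentence says that a visit-3 label ends follow-up. The 12-month minimum is a separate requirement, and a patient last seen on day 261 would fail it. The weight-bearing item is worded as status at 1 year and is not tied to visit 3. Later visits, remote contact and recorded event start dates allow later events to be captured and placed in time. The assignment rules may also be in the full protocol, which is not shown.

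Much of this stands, and it rules out several stronger readings that a reader might infer:
- **That 12 months of follow-up will not be delivered, or that early attenders are declared complete.** The text says neither. It only fails to ensure the minimum.
- **That the 1-year item is scored at visit 3.** Early recording is possible but not prescribed; the article does not name the contact that supplies the item.
- **That two complications are tied to 1 year.** Grammatically, only weight bearing clearly is. Whether the time point also governs ongoing pain medication is unclear.
- **That the label itself causes an undercount of known size.** A patient last seen on day 261 contributes the same events and the same denominator unit under either label. The loss comes from when contact ends, and any percentage rests on assumed inputs.

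What the reply does not remove is the gap between printed statements. The minimum and the site criterion state an intention, but the schedule, the optional later visits and the trigger for remote contact do not secure it. The analysis section does limit withdrawn patients to their time in the study. However, the complication denominator is explicitly the whole population, and a patient whose routine visits simply end early has not withdrawn.

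**Conclusion.** The point holds as a lack of reconciliation within the article. The 12-month label covers 8.6 to 15.0 months. Nothing printed requires a contact at or after 1 year when visit 3 falls early. The stated minimum is therefore not guaranteed, and "inability to bear full weight 1 year after definitive treatment" can be recorded up to 104 days early if day 0 is the day of definitive treatment, and earlier still if day 0 is a prior stage. Events after an early last contact drop out of the complication rates without adjustment.

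The figure of 104 days follows from Table 2 alone. The staging figures depend on an assumed interval. The size of the loss in complication rates cannot be derived from the document. The conclusion assumes that the full protocol adds no rule on completeness or on scoring the 1-year item; if it does, the article should state it.

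**What to change.** 1. Keep the Table 2 windows, and say that they serve only to label visits.
2. Define 12-month completeness and the 1-year weight-bearing item by the actual contact date, counted from definitive treatment: at or after 1 year, or within a margin stated in advance.
3. State whether the 1-year time point also applies to ongoing pain medication.
4. Extend the existing phone or e-mail contact to patients whose last visit falls before that point.
5. Where no such contact exists, treat the 1-year item as not assessed. Beside the crude complication rate, give an estimate of the 12-month rate censored at last contact.
6. Report the share of patients with contact at or after 1 year.

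**Cost.** Some additional phone or e-mail contacts, and some missing 1-year values that would otherwise have been filled from early visits. The remote contact becomes a registry-driven time point for early attenders, so the statement that no follow-up time points are dictated would need a short qualification. No extra clinic visit and no change in care is needed.

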### Outcome measures

The data collected in this registry will include treatment details, clinical outcomes, PROs, and procedure- or implant-related AEs. Documentation of treatment details will comprise information about the time from injury to index surgery, duration of surgery, number of stages of the procedure, skin preparation, tourniquet use, details about debridement and irrigation, type of reduction/fixation method, specifics related to the fixation devices (e.g., material type, implant dimension*)*, intraoperative blood loss, as well as the use of local agents to promote bone healing. Moreover, information relating to the perioperative use of either prophylactic or curative systemic antibiotics and application of local antimicrobials will be documented and entered in the database. Furthermore, information pertaining to soft-tissue management will be recorded, such as timing and details of wound closure, soft-tissue coverage, and flap type. For concomitant fractures of the tibia or fibula, the treatment method will be documented. If further treatments are performed during the index surgery, these will also be captured.

Clinical outcome documentation will include time to bone healing/union, the presence of malalignment, malrotation or malunion, and the time to full weight bearing. Time to bone healing is defined as the time elapsed between definitive treatment and bony union. The healing status assessment will be based on a combination of clinical and radiological parameters, which will be judged by the treating surgeon. Clinically, healing will be rated as complete when the patient is able to walk without support in the absence of pain or tenderness at the fracture site. Radiologically, the modified RUST score [18] will be determined by scoring each cortex on the anteroposterior (AP) and lateral radiographs as 1 = no callus, 2 = callus present, 3 = bridging callus, and 4 = remodeled, fracture not visible. The modified RUST score is the sum of these and therefore has a value from 4 to 16.

Malalignment, malrotation, and malunion will be determined by the treating surgeon. *Malalignment* will be measured on AP and lateral radiographs using the method described by Freedman et al. [19]. An angulation of > 5° in any plane is regarded as malalignment. *Malrotation* will be measured clinically and/or radiologically, depending on the availability of rotational CT and the local standard of care. A rotational deviation of > 10° is regarded as malrotation [20]. *Malunion* denotes that fracture-healing results in deformity corresponding to one or a combination of the following: > 5° malalignment, > 10° of malrotation, and/or a shortening of > 1 cm [20]. *Time to full weight bearing* is defined as the time elapsed between definitive treatment and the treating surgeon allowing the patient to bear full weight on the injured leg with or without any support. *Global health*, *pain interference*, and *physical function* will be documented using the corresponding domains of the Patient-Reported Outcomes Measurement Information System (PROMIS®) questionnaires. PROMIS® was established in 2004 with funding from the National Institutes of Health (NIH) as one of the NIH Roadmap initiatives for Medical Research and provided standardized and validated measures [21].

The questionnaires are designed to be completed by the patients without assistance. However, we anticipate that some patients may be unable to attend the planned FU visit(s). In these cases, patients will be contacted by e-mail or phone to document the outcome per interview. Interviews have been shown to produce similar scores compared to those obtained after completion of the questionnaires by the patients themselves [22, 23].

Validated translations of PROMIS® are available in an increasing number of languages. For this registry, only sites for which validated language versions are available will be asked to complete the forms. As other translations become available, these will be implemented immediately after notification of the respective IRB/EC.

The pre-injury status concerning global health and physical function will be captured retrospectively at baseline and entered in the database. The *global health assessment* reflects an individual’s evaluation of their physical, mental, and social health. In this registry, a short form of 10 questions (v1.2) will be used. The *pain interference* questionnaire covers pain interference with physical, social, and recreational activities and will be documented with a short form of 8 questions (v1.0 – Pain Interference 8a). The *physical function (mobility)* questionnaire assesses the patients’ ability to perform various daily living activities, documented in a short form of 10 questions (v2.0 – Physical Function 10b). *Pain* will be documented on a numeric rating scale (NRS) from 0 to 10 for the injured leg, the knee of the injured leg, and the ankle of the injured leg. *Procedure- or implant-related adverse events*, i.e., complications, will only be documented for the injured tibia, but not for concomitant fractures in the fibular, malleolar, or other regions.

In addition to AEs entered via free text, some pre-defined complications will be captured. *Intraoperative pre-defined complications* include iatrogenic fracture, iatrogenic vessel damage, excessive bleeding, iatrogenic nerve damage, and intraoperative resuscitation. *Postoperative pre-defined complications* include compartment syndrome, FRI, nonunion, refracture/peri-implant fracture, secondary loss of reduction, secondary displacement or breakage of the fixation material, deep vein thrombosis, pulmonary embolism, ongoing pain medication, or inability to bear full weight 1 year after definitive treatment.

FRI will be diagnosed as defined in the recently published consensus definition [24] and subsequent update [25]. Additional contextual information will be collected for all AEs and comprises the start date of the event, its severity and seriousness, information about the related additional treatment(s), date of recovery, and the event’s outcome.

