### Statistical analyses

As the registry aims are mainly descriptive and exploratory, patient characteristics and outcomes recorded at the standard of care scheduled FU assessments will be presented using simple summary statistics. Categorical variables will be summarized using the frequency and percentage for each category. Continuous variables will be summarized using the mean, standard deviation, median, interquartile range, and the minimum and maximum values. Additionally, summary statistics will be presented and stratified to clinically relevant categories, including the type of treatment received. Complications will be reported at both the patient and AE levels. Multiple events of the same type will be combined for each patient. Upon calculating complication rates, the denominator will be the total population size, irrespective of dropouts during FU. All complication rates will be presented with 95% confidence intervals. In addition to overall rates, complications will be presented according to categories for various relevant parameters, such as “action taken” (none/operative/nonoperative) or “outcome” (in progress/without persistent damage/with persistent damage/death). Patients with more than one event of the same type will be presented according to the most severe category.

To identify risk factors and evaluate specific research questions, it is planned to perform further appropriate statistics (e.g., multivariable analyses) if the volume and quantity of the collected data allows this. Enrolled patients who withdraw from the study FU for any reason (withdrawal of consent, death, loss to FU, etc.) will be included in the analysis until the time at which they withdrew.

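### Nonunion is divided by the total population although healing status needs a radiograph and an examination, so patients without a late assessment, including those reached only by phone or e-mail, count as non-events and bias the rate low

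*Protocol article*

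**What the plan says.** All references are to the protocol article.

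- **Healing status** (Outcome measures): "The healing status assessment will be based on a combination of clinical and radiological parameters, which will be judged by the treating surgeon". The clinical part asks for unaided walking and for no local pain or tenderness, the last of which needs an examination. The radiological part is a cortex-by-cortex score read from films in two planes: "The modified RUST score is the sum of these and therefore has a value from 4 to 16".
- **Availability of films** (Interventions and study procedures, Table 2 footnote on images, which covers X-rays and CT as well as photographs): "clinical pictures are collected ONLY if they are taken as part of the standard of care (routine) procedures".
- **Missed last visit** (Interventions and study procedures): for patients who cannot attend, "they will be contacted by e-mail or phone to document the final outcomes, especially patient-reported outcomes (PROs) and complications not previously captured". Outcome measures has a similar provision for missed planned visits in its questionnaire text, and the support it cites concerns questionnaire scores: "Interviews have been shown to produce similar scores compared to those obtained after completion of the questionnaires by the patients themselves".
- **Nonunion** is one of the pre-defined postoperative complications (Outcome measures). The article gives no separate definition or time point for it.
- **Rate** (Statistical analyses): "Upon calculating complication rates, the denominator will be the total population size", regardless of losses during follow-up, with a 95% confidence interval. The same section keeps withdrawn patients in the analysis only up to their withdrawal.

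**The concern.** The numerator of the nonunion rate can contain only nonunions that someone has established and recorded. The denominator contains everyone. Between the two lies a group whose healing status was never determined late in follow-up: patients who stopped attending, and patients whose last contact was a call or a message. The stated rule has no place for an undetermined status, so all of them lower the rate.

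What is at stake is the comparison between treatment strategies more than the overall percentage. The Discussion gives the association between treatment strategy and outcome as the registry's main purpose, and visits follow each site's routine. If attendance in person differs between sites or treatment groups, a difference in how often healing was assessed can look like a difference in nonunion. The planned confidence intervals do not reflect this error, and a larger sample does not reduce it.

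**Working it through.** **No plan figure to reproduce.** The sample size section states that there is no formal calculation. What follows is an illustration.

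**Inputs**

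- True nonunion rate p: 3% to 17% (Background). Central value (3 + 17)/2 = 10%.
- Population N: about 1000 (Sample size estimation).
- Share reached only remotely at the end, r: not given. Assumed 25%.
- Share of their nonunions not yet recorded at that point, u: not given. Assumed 50%, because Table 2 has earlier visits at 6 weeks and 6 months where some would already be known.
- Share of those unrecorded nonunions found by the remote contact, d: not given. Assumed 0 to 50%.
- Remote and attending patients are assumed to have the same true risk.

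**Step 1: rate under the stated denominator**

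Reported rate = p × [1 − r × u × (1 − d)]

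| p | d = 0 | d = 50% |
|---|---|---|
| 3% | 3 × (1 − 0.125) = 2.6% | 3 × (1 − 0.0625) = 2.8% |
| 10% | 10 × (1 − 0.125) = 8.75% | 10 × (1 − 0.0625) = 9.4% |
| 17% | 17 × (1 − 0.125) = 14.9% | 17 × (1 − 0.0625) = 15.9% |

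The relative loss is r × u × (1 − d), here 6.25% to 12.5%. At p = 10% and N = 1000, about 6 to 13 of 100 nonunions are missing. With d = 100% the loss is zero.

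**Step 2: where the bias comes from**

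If no call is made, nothing new is learned and the rate is the d = 0 value, 8.75%. If a call finds half of the unrecorded cases, the rate rises to 9.4%. The call moves the estimate towards the truth. The shortfall comes from keeping a patient of undetermined status in the denominator.

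**Step 3: comparison of two groups with equal true risk of 10%**

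Suppose the remote-only shares are 10% and 40%. These shares are chosen only to show the mechanism and have no source in the article. Again u = 50%.

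- d = 0: 10 × (1 − 0.05) = 9.5% against 10 × (1 − 0.20) = 8.0%, a spurious gap of 1.5 points.
- d = 50%: 10 × (1 − 0.025) = 9.75% against 10 × (1 − 0.10) = 9.0%, a gap of 0.75 points.

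**Step 4: what an assessed-only rate does**

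At p = 10%, r = 20%, u = 50%, d = 0 (Wilson 95% intervals):

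- Total population: 10 × (1 − 0.10) = 9.0%, interval 7.4% to 10.9%.
- Assessed only (80/800): 10.0%, interval 8.1% to 12.3%.

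The width goes from 3.5 to 4.2 points. In this case the total-population interval still covers 10%.

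The assessed-only rate is right only under equal risk and if entry to the denominator does not depend on the outcome. Return to r = 25% and N = 1000, and suppose remote-only patients are kept when a nonunion is on record and dropped otherwise. The rate is then (75 + 12.5)/(750 + 12.5) = 11.5%, too high, if none of the others had union documented earlier. This is why neither rate should stand alone.

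**The case against.** The strongest reply is that nothing in the article lets a phone call settle union. Outcome measures keeps healing status as the surgeon's clinical and radiological judgement and makes no exception for remote contact, so a patient without a film simply has no assessment at that time. The call is there mainly for patient-reported outcomes and complications not yet captured, and a nonunion diagnosed or reoperated elsewhere can be added through it. This stands. A reader might infer that a remote contact counts as complete follow-up, or that it is what turns a patient into a negative. The article supports neither: it does not define complete follow-up, gives the contact date no role in the analysis, and for the planned rate the call can only add events. Nor does it say that a remote contact dates bony union, so the point does not carry over to time to healing.

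A reader might also extend the argument to fracture-related infection. That does not follow from what is shown. Treatment for an infection is something a patient can report, and no effect on that rate has been derived.

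Other parts of the reply stand in part. Many patients will have union or nonunion established at an earlier visit and are not misclassified. Ongoing pain medication and inability to bear full weight at one year are themselves pre-defined complications, and a patient can report them and so prompt a diagnosis. The registry is mainly descriptive and exploratory. The definition of nonunion and the form fields may sit in the full protocol, which is not shown, so their absence from the article is no fault.

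None of this reaches the denominator. That rule is stated in the article, and if it is followed as written, patients of undetermined status lower the nonunion rate.

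**Conclusion.** The point holds as one about the denominator. Patients without a late radiographic and clinical assessment, whether lost or reached only remotely, enter the nonunion rate as non-events unless a nonunion is already on record or they report one. The direction is downward unless every unrecorded case is found by other means.

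The size cannot be determined from the article. At a true 10%, with 25% remote-only, half of their nonunions unrecorded and 0 to 50% of those found remotely, the reported rate is about 8.8% to 9.4%, a loss of 0.6 to 1.25 points. Only the range around the 10% has a source in the article. Larger losses need assumptions that the earlier scheduled visits and the purpose of the call make unlikely, such as every case unrecorded and none found remotely.

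For the overall rate, a loss of this size is smaller than the interval half-width in the example above. It matters more for comparisons between treatment groups or sites, where it distorts the contrast if assessment rates differ. Limiting the rate to withdrawn patients' time in the study would not be enough, because a patient reached by phone has not withdrawn, yet late healing status is still undetermined.

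**What to change.** Change the analysis rule for union and nonunion only:

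1. End follow-up at the last visit with both a radiographic and a clinical healing assessment, or at a nonunion diagnosis or reoperation reported remotely. Treat status after that point as not assessed, not as negative.
2. Report nonunion with the number assessed, or by a time-to-event method censored at the last assessment, and show it beside the total-population rate.
3. Tabulate the unassessed or remote-only share by treatment group and site, so that a reader can see whether a difference in nonunion follows a difference in assessment.

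Remote contacts remain valid for patient-reported outcomes and for events that a patient can report.

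The cost is analysis work and wording, with no change to patient care. Fewer patients count as assessed and intervals widen slightly (from 3.5 to 4.2 points in the example with 20% remote-only). The assessed-only rate may be too high if well-healed patients skip visits, or if remotely reported nonunions are counted while remote patients without one are censored earlier. Showing both rates makes that visible.
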